## Abstract

Patients with advanced non-small cell lung cancer (NSCLC) often experience burdensome symptoms, emotional distress, and poor quality of life (QOL). While national guidelines recommend early palliative care to address these supportive care needs, most patients with advanced NSCLC lack access to such comprehensive care. Our aim in the current study is to test a novel model of palliative care delivery and use of innovative technology to evaluate the feasibility, acceptability, and preliminary efficacy of a supportive care mobile application (app) for improving symptom management and adaptive coping in patients with advanced NSCLC. We will enroll 120 patients with unresectable Stage III or IV NSCLC diagnosed within the past 12 weeks receiving care with palliative intent at a major academic comprehensive cancer center and its community affiliates. The study will take place in two phases, the first of which will be dedicated to adapting an evidence-based, early palliative care treatment guide and prior supportive care mobile app intervention to address the specific symptom management and coping needs of patients with advanced NSCLC. The second phase of the study will be a two-group, randomized controlled trial. Study patients will complete baseline self-report measures of symptoms, mood, coping skills, and QOL, after which they will be randomized to receive either the mobile app intervention combined with usual oncology care or usual oncology care alone. Intervention patients will use a tablet computer to self-administer the mobile app, which consists of six modules that teach evidence-based skills for managing burdensome symptoms and coping effectively with advanced cancer and its treatment. At 12 weeks follow up, patients in both groups will repeat the same self-report measures. We will use descriptive statistics to determine feasibility metrics of enrollment and retention rates. For secondary self-report measures, we will use linear regression controlling for baseline values. The results of the present study will contribute to a growing body of evidence regarding the supportive care needs of patients with advanced cancer and will have implications for how best to use innovative technology to widely disseminate comprehensive supportive care services to all patients who may benefit.

**Clinical Trial Registration:** [www.ClinicalTrials.gov], identifier[NCT04629300].

## Introduction

1.

Despite remarkable breakthroughs in cancer therapeutics prolonging survival, many patients with advanced lung cancer continue to experience high symptom burden, psychological distress, and poor quality of life (QOL; Morrison et al., 2017). To address these unmet supportive care needs, our multidisciplinary research team of clinician scientists who specialize in thoracic oncology, palliative care, and clinical psychology has been investigating the effects of integrating palliative care in the outpatient oncology setting for patients with advanced lung cancer. Multiple randomized trials and follow-up studies have demonstrated the positive effects of this integrated model of care on patient QOL, mood symptoms, prognostic awareness, and quality of end-of-life care (Temel et al., 2010, 2011, 2017; Greer et al., 2012). Moreover, the beneficial effects of the early, integrated palliative care intervention on QOL and mood symptoms appear to be accounted for by improvements in patients’ use of adaptive coping skills (Greer et al., 2018). Descriptive analyses of clinician documentation regarding topics addressed during outpatient palliative care visits from prior trials indeed confirm that the top two primary foci were symptom management and helping patients cope effectively with cancer and its treatment (Hoerger et al., 2018).

However, the field of supportive oncology has failed to translate evidence-based interventions, such as early, integrated palliative care, from randomized controlled trials into disseminated clinical services that are widely accessible and tailored to the unique experiences of patients and caregivers. Only a minority of patients with cancer and their caregivers receive or have access to supportive care, including early, integrated palliative care services (Sullivan et al., 1702; Dionne-Odom et al., 2018). Moreover, a retrospective cohort study using the SEER-Medicare linked database revealed that, from 2000 to 2009, rates of palliative care consultations for patients with advanced cancer only increased from 3.0 to 12.9% despite guidelines that recommend palliative care for all patients (Roeland et al., 2016; Ferrell et al., 2017). Most of these consultations occurred in the inpatient setting (83%) and during the final month of life (77%; Roeland et al., 2016). A major barrier to the dissemination of early, integrated palliative care is the lack of specialty trained clinicians available to provide this high quality, evidence-based intervention (Lupu, 2010; Lupu et al., 2018).

Mobile applications (apps) offer a useful approach for enhancing the accessibility and scalability of interventions addressing the supportive care needs of patients who cannot access health care clinicians with necessary expertise. Once patients receive appropriate instructions on their use, mobile app interventions are highly acceptable to patients regardless of their age, health literacy, or computer experience (Vernon, 2010; Basch et al., 2016). Moreover, the growing use of mobile apps across various age, ethnic, and socioeconomic groups has started to reduce the “digital divide” observed in prior studies of interventions administered through the internet on desktop computers (Carroll et al., 2017). Mobile behavioral interventions have shown promising efficacy in addressing a variety of health problems including depression, anxiety, substance use disorder, and insomnia in the general population and in patients with psychiatric conditions (Bewick et al., 2008; Andersson and Cuijpers, 2009; Cuijpers et al., 2009; Ritterband et al., 2009; Vernon, 2010; Mohr et al., 2013; Cuijpers et al., 2014). While some studies of behavioral web-based and mobile interventions have demonstrated low adherence, mobile apps that incorporate features to enhance patients’ engagement including the use of tailored logic, educational games (i.e., gamification), adaptive skill-building, and a record of personal progress through the app content, have shown greater than 85% usability and retention rates (Payne et al., 2015). To overcome the challenges due to limited access to supportive care for patients with advanced cancer, our multidisciplinary research team has begun to develop and test the use of mobile apps. These apps include interventions based on CBT, psychoeducation, and behavioral self-management aimed at improving outcomes such as anxiety, symptom burden, and adherence to oral chemotherapy. The results from these trials showed that participants with worse baseline distress or adherence problems benefited most from the mobile app interventions (Fishbein et al., 2017; Greer et al., 2019, 2020).

Thus, the primary aim for the present study is to develop a novel supportive care mobile app by adapting our team’s existing mobile app interventions to address the specific symptom management and coping needs of patients with advanced NSCLC. We will examine the feasibility, acceptability, and preliminary efficacy of the mobile app to improve symptoms, coping skills, and QOL in patients with advanced NSCLC. We also aim to understand patients’ general perceptions of the mobile app and their overall satisfaction with the intervention by conducting qualitative exit interviews at the end of the study.

## Methods and analysis

2.

### Design

2.1.

The proposed study includes two phases for (a) mobile app development and refinement and (b) pilot efficacy testing. The first preliminary phase was dedicated to adapting our evidence-based, early palliative care treatment guide and prior supportive care mobile app interventions to address the specific symptom management and coping needs of patients with advanced NSCLC (Jacobsen et al., 2021). Our team’s prior research on mobile app interventions, specifically adapted to other populations of patients with advanced cancer, focused largely on addressing physical symptoms and emotional well-being. While patients with NSCLC do similarly experience obstacles across these domains, we have also found that they face challenges regarding their social, functional, and existential well-being. Given their complex and broad care needs across multiple domains, our research team comprised of clinician scientists with expertise in thoracic oncology, palliative care, and clinical psychology specifically designed and tailored our app to address each of these domains. We collaborated closely with a mobile app development and design company to create, refine, and finalize the supportive care mobile app, called “THRIVE.” We met with this technology partner weekly for approximately 1 year and communicated regularly online over Basecamp to review and refine scripted content for each learning module as well as illustrative graphics and interactive exercises to enhance patient engagement with learning the coping skills and symptom management strategies. Each module was constructed based on evidence-based psychoeducation, CBT, and acceptance and commitment therapy (ACT) principles. We completed the development and programming of all the THRIVE mobile app modules, and we conducted extensive user testing to identify and resolve any bugs, glitches, graphic errors, or other performance issues. Table 1 outlines the domains of the supportive care modules and corresponding skills-based interventions that the app includes. This phase was completed by September 2021.

**Table 1 tab1:** THRIVE mobile app components.

Module	Content
Introduction	Learn about the features, functionality, and components of the THRIVE app Review ‘roadmap’ of key medical milestones from diagnosis through phases of treatment for advanced non-small cell lung cancer Meet clinician guide for the app and watch patient personal narrative video
Physical Domain (“Health”)	Identify and evaluate symptoms Learn to communicate effectively with oncology team about symptoms Apply helpful self-management strategies for coping with symptoms
Social Domain (“Relationships”)	Clarify types of social support needs related to coping with cancer Identify those who can help meet those needs Learn effective communication skills to ask others for help
Emotional Domain (“Emotions”)	Identify the range of cancer-related worries and emotions Practice skills for coping with uncertainty about the future Learn to overcome avoidance behaviors and to foster positive emotions
Functional Domain (“Lifestyle”)	Identify patterns in energy and stamina during treatment Practice skills for managing energy fluctuations and improving self-care Learn to prioritize and pace activities as needed to achieve valued life goals
Existential Domain (“Reflection”)	Reflect on life history, relationships, and goals Participate in activities that increase meaning and purpose in life despite cancer Learn to talk with the oncology team about how to prepare for the future

The second phase consists of a multi-site pilot randomized controlled trial in a sample of 120 patients with advanced NSCLC to assess the feasibility, acceptability, and preliminary efficacy of the THRIVE mobile app intervention for improving patient-reported symptoms, coping, and QOL compared to usual oncology care. Enrolled patients are randomized in 1:1 fashion and stratified by study site (i.e., Massachusetts General Hospital [MGH] Cancer Center, Dana-Farber Cancer Institute, and four community affiliates) to receive either the THRIVE mobile app combined with usual oncology care or usual oncology care alone. After enrollment, participants complete baseline self-report measures regarding their symptoms, mood, coping behaviors, and QOL, which they repeat at 12 weeks post baseline. We also conduct qualitative exit interviews with up to 30 patients who are randomized to the mobile app intervention to understand and assess patients’ experiences using the THRIVE app.

### Selection/treatment of subjects

2.2.

#### Screening for eligibility

2.2.1.

Trained RAs screen the oncology clinic schedules at the study sites to identify potentially eligible patients. The target sample is 120 patients with newly diagnosed advanced NSCLC. Once a patient is deemed eligible in the screening process and approval is obtained from their treating oncologist, the RA approaches the patient in a private clinic setting at their next oncology visit or *via* telephone to describe the study, confirm eligibility, and complete informed consent procedures. The research team also may provide study information to eligible patients *via* a secure patient portal, using templated language. Specifically, patients receive a summary of the study and are encouraged to contact the research team if interested in learning more about participating in the study.

Participant inclusion/exclusion criteria are as follows:

##### Inclusion criteria

2.2.1.1.

Age ≥ 18 years.Diagnosed with unresectable Stage III or IV NSCLC in the past 12 weeks and receiving care with palliative intent.Eastern Cooperative Oncology Group (ECOG) Performance Status = 0–2 (with 0 indicating that the patient is asymptomatic, 1 that the patient is symptomatic but fully ambulatory, and 2 that the patient is symptomatic but in bed < 50% of the day; Cella et al., 2022).Plan to receive oncology care at one of the participating study sites.Ability to read and respond to questions in English.

##### Exclusion criteria

2.2.1.2.

Significant uncontrolled psychiatric disorder (e.g., psychotic disorder, bipolar disorder, major depression) or other co-morbid disease (e.g., dementia, cognitive impairment), which the treating oncology clinician reports would prohibit the ability of the patient to participate in study procedures.

#### Registration and randomization

2.2.2.

Enrolled patients are registered in the Clinical Trials Management System, OnCore, as required by Dana-Farber/Harvard Cancer Center standard operating procedures. Once the patient has been registered, a member from the MGH Cancer Outcomes Research and Education Program (independent from the study staff) performs randomization procedures using a predetermined computer-generated randomization schema developed and stored independently from the study team with 1:1 allocation, stratified by study site. Given the interventional nature of the study, neither participants nor study staff are blinded to group assignment.

### Interventional methods

2.3.

Upon study enrollment, participants complete baseline self-report measures, after which they are randomly assigned to either the THRIVE mobile app (intervention) with usual oncology care group or the usual oncology care alone group (control).

#### Intervention group

2.3.1.

For patients randomized to the THRIVE intervention, the RA provides them with a study-issued tablet computer from which the participants access the mobile app or assists the patient in downloading the app onto a suitable device already owned by the participant. The mobile app is optimized for the iOS operating system. The RA provides intervention patients with a comprehensive tutorial and detailed instructions regarding how to use the app and is available throughout the study to provide technological support if needed. Intervention patients also receive a handout with application download instructions, an informational video sent securely *via* email, and a user guide. Patients complete the mobile app intervention modules at their desired pace over approximately 10 weeks. The app prompts patients with reminders to complete their modules and utilizes incentives to enhance patient engagement. Table 1 details the components of the THRIVE mobile app modules. The mobile app electronically collects data on intervention fidelity (e.g., the number of completed modules, proportion of each module completed, time spent on each module, etc.).

Finally, we conduct qualitative interviews with up to 30 patients who are randomized to the intervention group to learn about their experiences with the THRIVE mobile app. We purposively sample patients to ensure adequate representation based on age and gender. The semi-structured interviews are conducted after the 12-week post assessment time point.

#### Usual oncology care group

2.3.2.

Patients assigned to the usual oncology care group receive standard cancer care without the THRIVE mobile app. As part of usual care, we query the electronic health record to track and record participant use of any supportive care services, such as social work, psychology, psychiatry, and palliative care. While we expect the referral and use of these services to be low and balanced between study groups, we will include these variables as covariates in the outcome analyses as needed.

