#### Self-report measures

2.3.3.

The study staff administers the following validated, self-report questionnaires at baseline prior to randomization and at approximately 12 weeks (+/− 2 weeks) after baseline. Participants are given a four-week time frame surrounding the 12-week time point to complete the measures. This window, which has consistently been used by our research group, allows for greater flexibility for participants to complete these measures given their degree of medical morbidity. These measures can be administered *via* paper hard-copy or electronically using Research Electronic Data Capture (REDCap), a secure, online HIPAA-compliant survey tool (Harris et al., 2009). The RA asks study participants to complete questionnaires in-person during clinic visits, *via* email, or over the telephone if necessary.

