Socio-demographic characteristics: Participants self-report their gender, race, ethnicity, marital status, education level, employment status, income, and frequency of technology use on a demographic questionnaire.Quality of life: Functional Assessment of Cancer Therapy-Lung (FACT-L; Cella et al., 1995). The FACT-L consists of four subscales assessing physical, social, emotional, and functional wellbeing during the past week. The instrument also contains the Lung Cancer Subscale (LCS), which evaluates specific symptoms related to lung cancer. Scores range from 0 to 5 on each item and the total scale score ranges from 0 to 136 with higher scores indicating better QOL.Symptoms: MD Anderson Symptom Inventory (MDASI; Cleeland et al., 2000). The MDASI is a 19-item survey, which consists of two subscales to assess cancer-related symptom severity and interference with daily activities on a 0–10 scale, with higher scores indicating worse symptoms.Mood: Hospital Anxiety and Depression Scale (HADS; Zigmond and Snaith, 1983). The 14-item HADS includes two subscales that measure anxiety and depression symptoms in the past week. Scores range from 0 to 21 on each subscale, and a threshold of > 7 on either subscale indicates clinically significant anxiety or depression symptoms.Coping strategies: Brief COPE Questionnaire; (Carver et al., 1989; Carver, 1997). The Brief COPE consists of 28 items assessing diverse coping methods on 14 subscales (e.g., active coping, use of emotional support, positive reframing, acceptance, behavioral disengagement, denial, and self-blame). Each item is scored on a 4-point Likert scale, with each subscale ranging from 0 to 8. Higher scores indicate higher use of that coping strategy. To reduce participant burden, we modified the questionnaire to consist of 8 subscales (Hagan et al., 2017).Supportive care service use: The Supportive Care Service Use Questionnaire (SCSUQ) includes two items that measure a patient’s use of mental health services, integrative medicine interventions, palliative care, and spiritual support over the past month.Mobile App Usability (intervention group only at week 12): The System Usability Scale (SUS; Bangor et al., 2008). The 10-item SUS evaluates patients’ subjective assessment of a product’s usability and acceptability.Perceptions and satisfaction with the mobile app (up to 30 intervention participants): Using a semi-structured qualitative interview guide, we assess patients’ experiences and satisfaction with the mobile app intervention.

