To our knowledge, the proposed study is the first that aims to examine the integration of a mobile app intervention into comprehensive care for patients with advanced lung cancer. Further, our app is the first of its kind to address and intervene upon multiple domains of quality of life that have not previously been targeted in patients with advanced cancer, such as social, functional, and existential wellbeing. The use of mobile app interventions, such as THRIVE, possess great promise for broad dissemination of evidence-based supportive and palliative care interventions in a timely, scalable, convenient, and potentially cost-effective manner. More specifically, mobile apps offer a useful approach for increasing accessibility for patients without creating an additional need for specialty-trained clinicians, which remains one of the major barriers to patients receiving such supportive care (Lupu, 2010; Lupu et al., 2018). Further, mobile apps can be implemented in a variety of care settings from large, academic medical centers to community oncology practices, reaching a wide array of patients with unmet needs. Their use may also reduce cost and staff resources dedicated to scheduling and providing in-person palliative and supportive care given the remote and asynchronous nature of the technology. Additionally, their integration may prove helpful for patients who face barriers to receiving in-person, clinic-based services given the degree of morbidity in the patient population or due to logistical challenges such as transportation.

It is important to note several limitations of the above protocol. First, only patients with advanced NSCLC are recruited to the study, and enrollment takes place at large academic cancer centers and their affiliates; thus, generalizability may be limited with respect to other disease groups or patients receiving care in other settings, such as stand-alone community oncology clinics. Further, only English-speaking patients are enrolled in the study, which ultimately may limit generalizability to patients of other racial or ethnic backgrounds. Additionally, the design of the present study precludes our ability to blind participants during study procedures or randomization. Also, despite efforts to maximize patient engagement with the intervention, it is possible that varying levels of technologic comfort between participants may affect the results.

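### Outcome models may be adjusted, as needed, for supportive-care use most naturally read as recorded after randomisation; if use differs between arms, the secondary app-effect estimates could be biased in either direction

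*Protocol article*

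**What the plan says.** Section 2.3.2 (Usual oncology care group) of the protocol article says "we query the electronic health record to track and record participant use of any supportive care services". It then states that "we expect the referral and use of these services to be low and balanced between study groups" and, in the same sentence, that "we will include these variables as covariates in the outcome analyses as needed". It gives no time window for the record query and does not define the condition for adjusting.

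Section 2.4 (Data analysis) describes the outcome models separately: the week-12 score regressed on group and the baseline value of the same outcome. Its own conditional adjustment covers only imbalances in baseline characteristics.

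Self-reported service use is also collected. The SCSUQ in section 2.3.3 covers "use of mental health services, integrative medicine interventions, palliative care, and spiritual support over the past month" and, like the other questionnaires there, is given "at baseline prior to randomization and at approximately 12 weeks (+/− 2 weeks) after baseline". A version from before randomisation therefore exists.

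Two other places bear on whether the app could change service use. Table 1 lists "Learn to communicate effectively with oncology team about symptoms" among the app's content. The Discussion says of mobile apps: "Their use may also reduce cost and staff resources dedicated to scheduling and providing in-person palliative and supportive care".

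**The concern.** Randomisation protects a comparison adjusted for baseline variables. It does not protect one that conditions on something that happens after allocation and may respond to it.

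Section 2.3.2 is most naturally read as concerning such a variable. Tracking use as part of usual care, and asking whether it is balanced between groups, both describe follow-up. Section 2.3.4 lists supportive-service use beside emergency visits, hospitalisations and hospice referral. Section 2.4 already has a rule for baseline imbalance, so the clause in 2.3.2 is a second and wider one.

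Two mechanisms can then move the estimate:

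- **Mediation.** If the app leads patients to services that help them, adjustment removes that part of the benefit. The Introduction itself credits integrated palliative care with better QOL and mood.
- **Shared causes.** Patients who deteriorate may use more services and also score worse at week 12. Comparing the arms at equal service use then compares patients with different prognoses.

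The likely trigger makes this worse. If the plan adjusts when use is unbalanced, it adjusts when the distortion is present, and leaves the model alone when adjustment would be harmless. The trigger is also undefined, in a trial whose staff are not blinded.

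At stake are the week-12 comparisons of FACT-L, MDASI, HADS and Brief COPE, and the effect sizes that section 2.4.1 intends for powering later trials.

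**Working it through.** **1. The plan's own figure.** Inputs from section 2.4.1: 120 patients, 10% attrition, 0.54 SD, 80% power. Section 2.2.2 gives 1:1 allocation. Two-sided alpha 0.05 is assumed, as sidedness is not stated. Evaluable patients: 120 × 0.90 = 108, or 54 per arm. Required n per arm = 2 × (1.960 + 0.842)² / 0.54² = 15.70 / 0.2916 = 53.8, so 54. Power with 54 per arm is 80.1% (normal) or 79.4% (t-test). The stated figure reproduces, and leaving service use out of the model does not change it.

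**2. Assumed inputs for the bias.** The article gives no service-use rates and no effect of services, so everything here is an assumption:

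- the true total effect of assignment is 0.54 SD;
- the week-12 score depends on baseline (coefficient 0.5) and on unmeasured decline U (coefficient −0.6 per SD), with residual variance set so that these parts sum to 1;
- service use is yes/no, with proportion p_C in controls and p_T with the app;
- services change the outcome by d SD;
- the latent tendency to use services correlates r with U.

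**3. Formula.** In large samples, adding service use M to the model moves the arm coefficient by

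shift = −b × (p_T − p_C), with b = d − 0.6 × r × f / v,

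where b is the within-arm slope of the outcome on M, f is the mean over arms of the standard normal density at the cut-off giving proportion p, and v is the mean over arms of p(1 − p).

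Worked case, 10% v 20%: f = (0.1755 + 0.2800) / 2 = 0.2277 and v = (0.09 + 0.16) / 2 = 0.125.

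- Mediation only (d = 0.5, r = 0): b = 0.5; shift = −0.5 × 0.10 = −0.050.
- Shared cause only (d = 0, r = 0.5): b = −0.6 × 0.5 × 0.2277 / 0.125 = −0.547; shift = +0.055.

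**4. Results (shift in SD around 0.54).**

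| Use, control v app | Mediation only (d = 0.5, r = 0) | Shared cause only (d = 0, r = 0.5) | Both (d = 0.3, r = 0.5) | Both (d = 0.5, r = 0.5) |
|---|---|---|---|---|
| 10% v 10% | 0.00 | 0.00 | 0.00 | 0.00 |
| 10% v 15% | −0.025 | +0.028 | +0.013 | +0.003 |
| 10% v 20% | −0.050 | +0.055 | +0.025 | +0.005 |
| 10% v 30% | −0.100 | +0.105 | +0.045 | +0.005 |
| 20% v 40% | −0.100 | +0.100 | +0.040 | 0.000 |

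Simulation with 1,000,000 patients per scenario agrees to within about 0.001. With a 20-point gap the adjusted estimate runs from 0.44 to 0.65 SD. When both mechanisms act they partly or wholly cancel. If the app lowers service use, the gap changes sign and so does every shift.

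**5. Consequence for planning.** Using n per arm = 15.70 / effect²: 0.54 SD needs 54; 0.44 SD needs 15.70 / 0.1936 = 81.1, so 82; 0.65 SD needs 15.70 / 0.4225 = 37.2, so 38.

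**The case against.** The strongest defence is that the clause may never operate. It is conditional, the protocol expects low and balanced use, and the outcome models in section 2.4 contain no service-use term. With balanced use the shift is zero; with a 5-point gap it is at most about 0.03 SD. The standard error of a mean difference with 54 per arm is about √(2/54) = 0.19 SD before baseline adjustment, so even a 0.10 SD shift lies within sampling noise. All of this stands, and it limits the severity. It does not rescue the rule, because the rule matters only if the expectation of balance fails, and bias does not average out as sampling error does.

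It can also be said that under pure mediation the adjusted coefficient is a legitimate direct effect. That is correct, but it is not the effect of offering the app, and under shared causes it estimates neither quantity.

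A reader might infer three stronger things that the article does not support:

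- **That the app is designed to change service use.** Nothing names this as a target. Table 1 makes a rise plausible, and the Discussion makes a fall plausible.
- **That the estimates will be biased.** That requires use to differ between arms, and the protocol expects otherwise.
- **That the randomised comparison is lost.** Nothing says an adjusted model replaces the one in section 2.4.

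**Conclusion.** The point holds as a moderate one. Section 2.3.2 states a rule that permits outcome models to condition on service use most naturally read as recorded after randomisation, with an undefined trigger that probably operates when use differs between arms. In that case the adjusted coefficient no longer estimates the total effect of assignment and could be biased in either direction.

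The size is unknown, because the documents give neither service-use rates nor service effects. The range from nil to about 0.10 SD covers gaps from 0 to 20 points under the stated assumptions; a 20-point gap is an assumption that goes against the protocol's own expectation. The conclusion also rests on reading the record query as covering follow-up, which the wording favours but does not state.

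Only the secondary patient-reported outcomes, and the effect sizes taken from them for the next trial, are exposed. The primary feasibility endpoint is untouched, so this is not a must-fix.

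**What to change.** In section 2.3.2, remove the covariate clause or restrict it to service use before randomisation. Either health-record use before randomisation or the baseline SCSUQ would serve. The SCSUQ is only a partial substitute, since its listed services do not name social work.

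In section 2.4, state that the outcome models contain baseline covariates only. Report service use during follow-up by arm as a process measure. Label any model that includes it as exploratory or as a mediation analysis, shown beside the randomised estimate and not in its place. Take effect sizes for the next trial from the baseline-adjusted model.

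The cost is a sentence or two of text. The health-record query and the SCSUQ are already planned, so no new data are needed, and neither N = 120 nor the stated power changes.
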